#### Plans to Promote Participant Retention and Complete Follow-Up

TLM Nigeria has a meal subsidy program for all in-patients at The Leprosy Referral Hospital, Chanchaga. The meal subsidy program will continue through the period of this study. It is expected that the meal subsidy program will be sufficient to keep the patient at the hospital from the period of admission up to the time of discharge. Phone contacts of participants or their close relatives will be collected and used for postdischarge follow-up.

#### Data Management

All data generated from this study will be classified according to the University of Birmingham Information Security Framework. All data will be collected and stored electronically to reduce data entry errors, such as contradicting answers. Data will be reported on an electronic case report form, and all local staff will be trained to collect data directly onto electronic tablets. Data will be acquired and stored on the REDCap database platform, with access restricted by passwords at both the University of Ibadan and the local site in Nigeria. Each participant will be allocated a unique study number when they agree to participate (and before randomization), which will be used on all documents. A master list linking a trial participant number to their identity (name) will be retained by the hospital securely in a locked filing cabinet. This is necessary so that the notes of any person who withdraws consent for data storage can be removed. The trial participant master list will be stored separately from patient lists and the trial data.

#### Confidentiality

Participant confidentiality will be ensured throughout the study and no participant-identifying information will be released to anyone outside the project. Confidentiality will be secured through several mechanisms. Each participant will be assigned a study subject ID, which will be used on all study forms. Any study forms and paper records that contain personal identifier information (eg, address lists and phone lists) will be kept secured and locked at the trial sites. Access to all participant data and information at the sites will be restricted to authorized personnel.

Participants will not be identified by name in any reports or publications, nor will the data be presented in such a way that the identity of individual participants could be inferred. Analysis files created for further study by the scientific community will have no participant identifiers. The trial data will be kept under lock for up to 10 years, after which they will be destroyed. Only authorized persons will be granted access to the trial data.

#### Plans for Collection, Laboratory Evaluation, and Storage of Biological Specimens for Genetic or Molecular Analysis in This Trial or for Future Use

At the pre-enrollment stage, we will collect a swab of the ulcer surface to examine the wound for bacterial infections. Afterward, we will not collect or retain biological specimens for any future use in this trial.

### Statistical Methods

#### Statistical Methods for Primary and Secondary Outcomes

Time to healing will be analyzed using a Cox proportional hazards model with and without adjustment for baseline characteristics (trial ulcer area and participants’ age), allowing for right censoring. For the rate of healing, we will define the outcome ulcer size in cm^2^ at each time point and include in the model time since admission, treatment status, and their interaction. We will analyze this model using a linear mixed-effects model with participant-level random effects and both with and without adjustment for participant characteristics. Given there are multiple clinical outcomes (2 outcomes, with and without adjustment), we will adjust reported *P* values for multiple testing using a step-down method, which provides an efficient means of controlling the family-wise error rate [22]. We will derive the approximate distributions of the test statistics to perform the step-down procedure using a permutation test approach, by simulating 10,000 rerandomizations of the individuals [23].

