### Trial Design

The study is a multicenter, prospective, single-blinded, parallel group, and 1:1 individually randomized controlled trial. The study duration is 48 months (maximum), with recruitment starting at month 5 and postdischarge follow-up starting at month 11. We aim to enroll between 90 and 130 participants over a 24-month recruitment period. The study pathway is shown in Figure 1.

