### Assignment of Interventions: Allocation

#### Sequence Generation

Participants will be enrolled sequentially, stratified by ulcer size (above or below 10 cm^2^) and randomly allocated (1:1) to undergo honey treatment or usual care with normal saline using a “digital sealed envelope” method [19].

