#### Concealment Mechanism

An allocation table will be generated remotely at the trials office at The University of Ibadan. A permuted block randomization method will be used to generate the randomization sequence within each stratum. Randomly selecting blocks of size 2, 4, 6, or 8 will be generated in order to maintain balance between the numbers allocated to each of the 2 groups and to ensure allocation concealment. The generated table will be uploaded into the REDCap database platform to be used for participant enrollment. Access to the allocation table will be restricted. Trial staff in Nigeria will not have access to the allocation table. When a participant’s details are submitted, the trial arm and a unique study number will be assigned and revealed to the local clinician so that the randomized group that the participant is assigned to cannot be altered.

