## Discussion

This study protocol describes a clinical trial with honey as an intervention for the dressing of leprosy ulcers. It is a single-center, comparative, prospective, single-blinded, parallel-group, and blocked-stratified randomized controlled trial.

Leprosy is regarded as a neglected tropical disease because of its near absence from the global health agenda [24]; as such, very little attention has been given to the treatment of ulcers in leprosy in spite of its debilitating nature and the social stigma it attracts. Methods such as laser therapy [25], zinc tape [26], pentoxifylline injection [27], amniotic membrane gel [28], phenytoin suspension [29], and leukocyte- and platelet-rich fibrin [3] have been tested on leprosy foot ulcers as the search for the most suitable treatment continues. Normal saline has been the most common comparator in most of the studies on ulcers in leprosy [30]. Among the challenge with the normal saline dressing are the slow rate of healing, the possibility of ulcers getting infected with pathogens [31], and the likelihood of the recurrence of treated ulcers. A Cochrane review [30] noted that previously published evidence is limited, due to a high or unclear risk of bias (selection, performance, detection, or attrition), imprecision due to the small number of participants, indirectness due to poor outcome measures, and inapplicable interventions.

Honey is considered as a cheaper and more readily accessible alternative treatment for many types of wounds. Although honey has been known for centuries to promote wound healing, there are only a few controlled clinical trials that assess its efficacy. While honey is noted to have wound healing properties, including debridement, deodorization, and antimicrobial properties [14], its use may result in painful sensation in about 5% of persons, although this is unlikely to occur in leprosy and diabetes [15]. The hypothetical risk of botulism will be mitigated by regularly screening the honey sample. Detailed procedures for the study have been described in this protocol. We expect that the outcome of this study will provide valuable evidence on the use of honey for the treatment of ulcers in leprosy.

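### Two hospitals recruit, but center is not a randomization stratum or a named Cox covariate: the comparison stays valid, at a possible cost in precision that adjustment would recover

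*Protocol article*

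**What the plan says.** **Number of centers.** The Trial Design section says: "The study is a multicenter, prospective, single-blinded, parallel group, and 1:1 individually randomized controlled trial". The Abstract and Study Setting name two hospitals, in Niger State and Cross River State. The Discussion says: "It is a single-center, comparative, prospective, single-blinded, parallel-group, and blocked-stratified randomized controlled trial". These statements conflict.

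**Randomization.** Sequence Generation names one stratification factor: "Participants will be enrolled sequentially, stratified by ulcer size", with the cut at 10 cm². Concealment Mechanism adds: "A permuted block randomization method will be used to generate the randomization sequence within each stratum", with randomly chosen block sizes of 2, 4, 6 or 8. Center is not mentioned.

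**Models.** Under Statistical Methods for Primary and Secondary Outcomes, time to healing is analyzed by a Cox model "with and without adjustment for baseline characteristics (trial ulcer area and" participants' age). The parenthesis reads as a complete list. The mixed model for ulcer size has time, treatment, their interaction and participant-level random effects, with and without participant characteristics that are not listed. P values come from 10,000 simulated rerandomizations.

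**Local conditions.** The section on participant retention says: "TLM Nigeria has a meal subsidy program for all in-patients at The Leprosy Referral Hospital, Chanchaga". It gives no corresponding information for the Ogoja hospital.

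**The concern.** Two hospitals in different regions, under different ownership and with different supporting organizations, may well heal ulcers at different rates. Center is then a prognostic factor known at randomization, and the stated strata and Cox covariates make no use of it. This is not merely a detail left to an analysis plan, because the article itself fixes the stratification factor and the Cox covariates.

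Three consequences are possible if healing differs by hospital:

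- The Cox hazard ratio from a model without center lies closer to 1 than the hazard ratio within hospitals.
- Power falls.
- If chance gives the arms different hospital mixes, the estimate of that one trial moves with the imbalance.

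The Sample Size section says that inference will rest on effect sizes more than on significance, so the size and precision of the estimate matter directly.

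**Working it through.** **Inputs from the Sample Size section.** 84-day healing of 70% against 90%, hazard ratio 1.91, two-sided 5%, power 80%, 1:1 allocation, log-rank test, 47 per group.

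**Step 1: reproduce the plan's figure.**
- HR = ln(0.10)/ln(0.30) = 1.912.
- Events by Schoenfeld's formula = 4 × (1.960 + 0.842)² / (ln 1.912)² = 74.7, so 75.
- Mean healing proportion = (0.70 + 0.90)/2 = 0.80. Then 75/0.80 = 93.75 participants, or 47 per group. The plan's figure is reproduced.

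**Step 2: chance imbalance without center stratification.** With a share *s* of participants at one hospital, the difference between arms in that share has SD = √(4s(1−s)/N). The split is assumed.

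| N | s = 0.5: SD (×1.96) | s = 0.7: SD (×1.96) |
|---|---|---|
| 90 | 0.105 (0.21) | 0.097 (0.19) |
| 94 | 0.103 (0.20) | 0.095 (0.19) |
| 130 | 0.088 (0.17) | 0.080 (0.16) |

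**Step 3: simulation at N = 94.** There were 1,000 trials per scenario, with permuted blocks of 2, 4, 6 or 8 within ulcer-size strata, exponential healing times censored at 84 days, and control healing held at 70% overall. Assumed: splits of 50:50 and 70:30, center HR of 1.5, 2 or 3, and 30% of ulcers above 10 cm². The treatment HR of 1.91 applies within hospital (log HR 0.647).

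To show what these center effects mean at a 50:50 split, let *x* be the unhealed control proportion at the slower hospital. Solving x + x^(center HR) = 0.60 gives control healing of about 63% against 77% (HR 1.5), 58% against 82% (HR 2) and 51% against 89% (HR 3).

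Ranges below run over the two splits.

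| Center HR | Mean log HR, no center | Power, no center | Power, center in analysis only | Power, center in randomization only | Power, center in both |
|---|---|---|---|---|---|
| 1.5 | 0.64 | 77-78% | 78-79% | 77% | 77-79% |
| 2 | 0.61-0.62 | 73-75% | 78-80% | 73-76% | 78-79% |
| 3 | 0.55-0.56 | 64-67% | 77% | 65-67% | 77-79% |

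The Monte Carlo error of a power figure near 78% is √(0.78 × 0.22/1000) = 1.3 points, so the center HR 1.5 row shows no clear difference. As hazard ratios, the attenuated means are exp(0.61) to exp(0.62), or 1.84-1.86 (center HR 2), and exp(0.55) to exp(0.56), or 1.73-1.75 (center HR 3), in place of 1.91. At N = 130, center HR 2 and a 50:50 split, power is 86.5% without center and about 90% with it.

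**Step 4: validity under no treatment effect.** Without center, the mean log HR is −0.007 to 0.001 and the rejection rate is 4.0-5.6%.

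**Step 5: shift in a single trial.** An imbalance of 10 points or more occurs in about 29-38% of simulated trials, and 20 points or more in about 2-6%. The log HR moves by 0.28 to 1.10 per unit of imbalance across scenarios. A 10-point imbalance therefore multiplies the HR by exp(0.028) to exp(0.110), or 1.03-1.12. A 20-point imbalance multiplies it by 1.06-1.25. The standard error of the log HR is about 0.24, so one standard error multiplies the HR by exp(0.24) = 1.27.

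**The case against.** The strongest reply is that nothing here is invalid. Randomization protects the comparison without center, and chance imbalance is already part of the standard error and of the permutation distribution. A factor that was not used for stratification need not be adjusted for. Step 4 bears this out, and the reply stands: the gain is in efficiency. A reader might infer that imbalance between hospitals biases the trial. On average over randomizations it does not.

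The size is also uncertain. The document gives neither the split nor any center effect, and at a center HR of 1.5 the loss is negligible. This stands too; the large losses need a center HR of 3, for which the document offers no basis.

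Some stronger readings are tempting but lack support:

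- *That no primary model contains center.* This is established for the Cox model only. The mixed model's participant characteristics are unlisted and could include it.
- *That the mixed model's slope interval is widened.* This was not computed. Participant-level random effects largely absorb a difference in level between hospitals; a difference in slope would matter, and none is documented.
- *That the meal subsidy exists at one hospital only.* The article reports it for Chanchaga and is silent on Ogoja.
- *That healing is judged differently at each site.* The local clinician decides when treatment stops, but blinded assessors in Nepal measure photographs, and the Abstract has blinded observers determine the outcomes.
- *That the second hospital was added without revising the statistics.* The single-center wording is compatible with this but does not show it.
- *That the rerandomizations ignore blocks or strata.* The word used does not imply that.

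**Conclusion.** The point holds as a matter of efficiency and reporting. Center is absent from the stated strata and from the Cox covariates, and is unspecified in the mixed model. The planned comparison remains valid.

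Under the assumptions of Step 3, omitting center costs nothing discernible at a center HR of 1.5, about 3 to 6 points of power at 2, and about 10 to 15 points at 3. It attenuates the hazard ratio correspondingly. Adjustment in the analysis alone recovers nearly all of this. Stratifying the randomization while leaving center out of the model does not.

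The contradiction between single-center and multicenter is in the text itself and depends on no assumption.

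**What to change.** Before anyone sees unblinded results:

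1. Stratify the Cox model by center, or add center as a covariate.
2. Name center and center × time as terms in the mixed model.
3. State that the 10,000 rerandomizations follow the actual scheme (permuted blocks within ulcer-size strata), and keep center in each refit.
4. Reconcile the single-center wording in the Discussion with the Abstract, Trial Design and Study Setting.

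The cost is one or two degrees of freedom and a few sentences, with no new participants. The article does not expressly say that center is a recorded field, so confirm this; each hospital enrolls its own patients, so it should be recoverable.

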### Objectives

The aim of this study, Honey Experiment on Leprosy Ulcer (HELP), is to evaluate the healing properties of raw, unadulterated African honey in comparison with normal saline dressing for the treatment of leprosy ulcers.

The study objectives are as follows:

Recruit 90‐130 eligible, consenting people within 12 months.Randomize the participants to receive ulcer dressing with either honey (intervention group) or normal saline (control group) twice a week.Observe the rate of healing based on 2 observations per week (cm^2^ per unit time, until either the ulcer has healed or 84 d have elapsed since randomization).Observe the time to healing, defined as complete re-epithelization (up to a maximum of 84 d).Monitor the rate of activity of study participants with pedometers.Monitor the recurrence of treated ulcers or appearance of new ulcers and any anatomical changes in the limb at 6-month follow-up after randomization.

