### Eligibility Criteria

The local, medically qualified researchers employed on the grant will screen all ulcer admissions. The researchers will complete web-based eligibility forms for each patient with an ulcer. Consent will be sought by the research fellow from consecutive patients aged ≥18 years with a foot or leg ulcer between 2 and 20 cm^2^ and not requiring surgery (eg, skin graft). The inclusion criteria are as follows:

Patients with a chronic foot ulcer of at least 6-week duration due to leprosy neuropathy.Patients ≥18 years of age.Ulcer with a surface area between 2 and 20 cm^2^ inclusive.Ulcer is clean, dry, and free from infection.Patient can provide informed consent.

The exclusion criteria are as follows:

Any significant medical condition, laboratory abnormality, or psychiatric illness that would prevent the participants from participating in the study.Ulcers with a surface area <2 or >20 cm^2^.Patient requires a skin graft.Any condition that confounds the ability to interpret data from the study (ie, patients with HIV or tuberculosis under active treatment).Any wound that has clinical microbial infections.Diabetes or diabetic ulcer.A patient has returned to the hospital having already taken part in the trial.

The wound dressing protocol for the HELP study is shown in Multimedia Appendix 1.

In the uncommon scenario where a participant has more than 1 foot ulcer, the largest ulcer will be selected as the index ulcer before randomization, and all ulcers will receive the same treatment (eg, if the participant is in the intervention group, all ulcers—not just the 1 being monitored for the trial—will be treated with honey). Observations will be made on all ulcers, but only the largest ulcer will be used in the primary analysis (see the *Discussion* section). Eligible patients will be offered entry in the trial at the point where their senior clinician judges them to be suitable for the honey treatment. This point arises once the lesion has been cleared of any debris or infection, typically by 7‐10 days after beginning treatment with or without antibiotic or debridement.

Swabs of the ulcer area will be taken to assess the wound for bacterial infections prior to the recruitment of participants into the study.

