### Additional Consent Provisions for the Collection and Use of Participant Data and Biological Specimens

The participant information sheet contains all information about the data to be collected and how the data will be stored and used. Biological specimens such as a swab of the ulcer surface will be obtained for the purpose of screening for bacterial infections prior to the recruitment of a participant into the study. Participants who refuse to give consent will continue to receive normal care from the hospital, but they will not be part of the study.

Participants can decide to withdraw their consent at any time during the study. Such participants will be given a form to complete, stating their reason for withdrawal. A participant may either withdraw fully or they may withdraw from treatment but consent to ongoing data collection.

Once a person consented to participate in the trial, baseline data will be collected. This will precede randomization.

Data will be collected directly onto electronic tablets, and the computer program (Research Electronic Data Capture [REDCap]; Vanderbilt University) will check the range of the information. Photographs of the ulcers will be captured using the tablet device. Each participant will be allocated a unique trial number, which will be included in all data entry forms and linked to the photographs. The level of activity (step count) will be recorded at each dressing change across both intervention and control groups until 84 days or discharge, whichever comes first. This date will enable us to check for postrandomization (“performance”) bias.

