### Outcomes

We define 2 main outcomes relating to ulcer healing. The main outcomes will be (1) rate of healing based on 2 observations per week (until healed or 84 d from randomization) and (2) time to healing defined as complete re-epithelization (up to 84 d). Secondary outcomes will be (1) the recurrence of treated ulcer and (2) appearance of a new ulcer. Long-term outcomes will be measured at the follow-up 6 months after randomization, which will be (1) the number of days hospitalized prior to discharge and in total (to include any readmission related to leprosy ulcers) by 6 months and (2) the number of visits to any health care facility from discharge to the end of follow-up at 6 months.

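### The rate-of-healing model counts time from admission although the outcome runs from randomization, and its random-effects wording does not secure participant-specific slopes

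*Protocol article*

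**What the plan says.** All references are to the protocol article.

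- **Outcome window.** Outcomes defines the first main outcome as "rate of healing based on 2 observations per week (until healed or 84 d from randomization". Objectives gives the unit and the same window: "cm^2^ per unit time, until either the ulcer has healed or 84 d have elapsed since randomization".
- **Model clock.** Statistical Methods for Primary and Secondary Outcomes takes ulcer size in cm² at each time point as the response and will "include in the model time since admission, treatment status, and their interaction".
- **Gap between the two origins.** Eligibility Criteria says that patients become suitable once debris or infection has cleared, typically 7-10 "days after beginning treatment with or without antibiotic or debridement". On baseline data collection, the consent section says "This will precede randomization".
- **Random effects.** The model is a "linear mixed-effects model with participant-level random effects", fitted with and without adjustment for participant characteristics. Intercepts and slopes are not named.
- **Inference.** P values come from 10,000 rerandomizations with a step-down adjustment. Sample Size says that the inferential approach rests on effect sizes and not on statistical significance. Interim Analyses applies the same methods at the interim look.

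**The concern.** The outcome and its model run on different clocks. With time zero at admission, the treatment main effect is a between-arm contrast before anyone was randomized, and day 84 on the outcome's scale is a different model time for each participant.

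The second issue is the random-effects wording. Ulcers heal at different speeds, so slopes vary between participants. A model with random intercepts alone treats repeated photographs of one ulcer as near-independent evidence about a common slope. It also gives most weight to long-stayers, because ulcers that heal leave observation early. Both the interval for the interaction and the interaction itself then depend on a choice that the text leaves open. This matters more here than in a trial that relies on a P value, because the protocol says it will interpret effect sizes.

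**Working it through.** **1. The plan's own figure.** Control healing is 70% and intervention healing 90% by day 84, so HR = ln(0.10)/ln(0.30) = 1.91. Schoenfeld's formula at two-sided 5% and 80% power gives 75 events. With a mean event probability of 0.80, 75/0.80 = 93.75, or 47 per group. The stated 47 reproduces. It is a log-rank figure; the article gives none for the rate-of-healing model.

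**2. The clock, by algebra.** Let t be weeks since randomization, d the delay from admission, and A the arm. On the admission clock with a straight line in time:

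b0 + b1(t + d) + b2·A + b3·A(t + d) = (b0 + b1·d) + b1·t + (b2 + b3·d)·A + b3·A·t

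For constant d, the interaction b3 is unchanged. The arm contrast at randomization is b2 + b3·d, so the reported main effect b2 differs from it by b3·d. If the fitted lines meet at randomization, b2 = -b3·d. Take the slope-model estimate from step 3, b3 = -1.195 cm²/week, and d = 7-10 days = 1.00-1.43 weeks, assuming that treatment begins at admission. The main effect would then be +1.20 to +1.71 cm², with no meaning as a treatment effect.

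**3. The clock, by simulation.** The runs used 47 per arm, 200 trials per scenario and HR 1.91. Assumptions not in the documents: entry area log-uniform over 2-20 cm², exponential healing times matching 70% and 90%, linearly shrinking radius and 10% measurement error. Interaction in cm²/week:

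| Delay | Random effects | Admission clock | Randomization clock | Calibrated power (admission / randomization) |
|---|---|---|---|---|
| 7-10 days | intercept | -0.156 | -0.156 | 0.175 / 0.175 |
| 7-10 days | intercept + slope | -1.195 | -1.197 | 0.355 / 0.360 |
| 3-28 days (assumed) | intercept | -0.166 | -0.170 | 0.215 / 0.220 |
| 3-28 days (assumed) | intercept + slope | -1.139 | -1.254 | 0.455 / 0.475 |

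Attenuation at 3-28 days is 1 - 0.1658/0.1702 = 3% and 1 - 1.1388/1.2535 = 9%. Power is unchanged within simulation error.

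**4. Random slopes.** Simulation B is the one in step 3 (randomization clock and 7-10 day delay unless a range is given). Simulation A used 47 per arm, about 240 trials, constant radius closure, a log-SD of healing time of 0.6 and 8% measurement error. The response is raw cm².

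| Quantity | A | B |
|---|---|---|
| Null, intercept only: true SD / mean model SE | 0.109 / 0.028 = 3.9 | 0.117 / 0.035 = 3.3 |
| Null, intercept only: Wald rejection | 64% | 54-56% |
| Null, with slopes: Wald rejection | 9% | 3% |
| Interaction at HR 1.91: intercept only, then with slopes | -0.20, then -0.46 | -0.156, then -1.197 |
| Size-calibrated power: intercept only, then with slopes | 28%, then 66% | 18-22%, then 36-48% |

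B's power ranges cover both delay scenarios. A further null run with exponentially declining area gave the same pattern: Wald rejection of about 56% with intercepts only and 6.5% with slopes. Monte Carlo error on the power figures is about 3-4 points, and more after calibration.

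**5. Baseline area x time.** Under constant radius closure, area is A0(1 - t/T)², so the average closure rate is A0/T. For the same healing time T, a 20 cm² ulcer closes ten times as fast in cm² as a 2 cm² ulcer. A baseline-area main effect shifts the level and leaves this slope variation in place. In simulation A, adding baseline area x time to the raw-area slope model raised calibrated power from 66% to 88%. Simulation B did not test this term.

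**The case against.** The case against has four parts.

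- **The clock does little harm to the estimate of interest.** The rate of healing is the interaction, and the delay arises before allocation, so randomization balances it. Also, the 7-10 days run from the start of treatment, which the article does not equate with admission. This stands. A reader might infer that the admission clock biases the treatment effect or costs power; steps 2 and 3 do not support that. The contradiction between the sections remains, as does the displaced main effect.
- **The text does not exclude slopes.** The wording is plural, and the covariance structure may be set in an analysis plan that is not shown. This stands too. A reader might infer that an intercept-only model with a 64% false-positive rate is planned. The documents do not say so, and that figure is a Wald rate, whereas the planned test is by permutation. Nor does the article say how intervals will be formed. What survives is conditional.
- **Raw cm² is the declared unit.** A reader might infer that a straight line in raw area is an error and that square-root area should replace it. The article states no functional form for time, and cm² per unit time is its own outcome. The square-root gain (94% calibrated power in A, 49-53% in B) is partly built in, because constant radius closure makes square-root area linear.
- **The power levels are unstable.** A and B agree on the ordering but differ widely in level. They do not establish that the trial is underpowered on this outcome.

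**Conclusion.** The concern holds in two parts of different strength.

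**Clock: an error in the text.** The model's time origin contradicts the outcome definition, and nothing else in the article reconciles them. The damage falls on the meaning of the treatment main effect and on the match to the 84-day window. The effect on the treatment-by-time estimate is about 0-9%, depending on an assumed spread of delay.

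**Random effects: open wording with a consequential choice.** If only intercepts were fitted, the model-based standard error of the interaction would be about 3-4 times too small, power would fall, and the estimate would differ by a factor of 2.3 (0.46/0.20) to 7.7 (1.197/0.156) from the slope model. Permutation corrects the P value but leaves the estimate and any model-based interval exposed. The direction is consistent across the assumed curves; the sizes depend on those curves.

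**What to change.** In Statistical Methods for Primary and Secondary Outcomes:

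1. Replace time since admission with time since randomization.
2. State a random intercept and a random slope on time for each participant.
3. In the adjusted model, include baseline ulcer area and baseline area x time.
4. Keep cm² as the response, in line with the declared outcome. A square-root-area model may be added as a sensitivity analysis, with results back-transformed to cm² at a few baseline sizes. It is an option and not a correction.

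No new measurements are needed: the 84-day window already requires the randomization date, and baseline data are taken before allocation. The model has more parameters and will take longer to refit in 10,000 rerandomizations. Because the interim analysis uses the same methods, the change should be recorded as an amendment and made without sight of comparative results. If the analysis plan already specifies slopes, only items 1 and 3 need action.
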